### Acupuncture

Acupuncture has been used to treat tinnitus for a long time. Neuroscience studies related the effects of acupuncture to neuronal stimulus, activation of endogenous opioid mechanisms and neuropeptides which stimulate specific brain structures [8]. It has been reported that acupuncture can yield immediate relief, both from the loudness and the disturbing quality of tinnitus, significant improvement in quality of life, less tension, and better sleep [9-12]. In contrast, an analysis of six randomized clinical trials of acupuncture for tinnitus failed to demonstrate any efficacy [13]. Based on the theory of traditional Chinese medicine (TCM), acupoints located on both the adjacent and distal area of the disease can be needled to treat disease. Furthermore, the way of combining these acupoints is often used for strengthening the curative effect.

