### Statistical methods

The trial aims to detect a difference in loudness and annoyance perception of tinnitus between the four study groups. This is deemed a clinically significant difference of average 20-point reduction on the VAS scores of loudness in acupuncture group when comparing with the sham-control group based on previously published studies [14]. The standard deviation is 25.9 in acupuncture group and 23.8 in the sham-control group, respectively, as previous studies have suggested [15].

The following formula was used for a four-group trial [16]:

(1)$$n1=n2=2{\left[\frac{\left(\mathrm{u\alpha}+\mathrm{u\beta}\right)s}{\delta }\right]}^{2}$$

Calculations are performed using 80% power, a 5% significance level (two-side). The required sample size is approximately 24 participants for each group. We plan to enroll a total of 112 participants with 28 in each group, allowing for a 25% withdrawal rate.

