### Data analysis

Data will be analyzed according to the 2×2 randomized factorial study designs. The statistical model includes two fixed factors (both local acupoints and distal acupoints). Interaction is evaluated using the interaction term in the ANOVA model and by visual assessment of profile plots. As no interaction between local acupoints and distal acupoints is detected, results are presented as a factorial design (for example, all patients receiving acupuncture at local acupoints in combination with distal non-acupoints; and all patients receiving acupuncture at local non-acupoints in combination with distal acupoints).

Data analysis will be conducted by statisticians who are independent from the research team. Every analysis is conducted using the SPSS software (SPSS 12.0 KO for Windows ©).

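### Factorial presentation hangs on no interaction being detected, a weak check in this trial, and the contrasts that answer its question can be replaced by averages

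*Protocol article*

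**What the plan says.** All references are to the protocol article. Under Interventions, four groups form a 2×2 design: A (both true point sets), B (true local, sham distal), C (sham local, true distal) and D (both sham).

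Data analysis plans a factorial ANOVA with two fixed factors and says: "Interaction is evaluated using the interaction term in the ANOVA model and by visual assessment of profile plots". The next sentence is: "As no interaction between local acupoints and distal acupoints is detected, results are presented as a factorial design". A bracketed example follows. It describes patients with true local and sham distal points, and patients with sham local and true distal points, which are groups B and C.

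The Abstract and the Discussion give the question as whether needling both sets works better than needling them separately. The Acupuncture section gives the rationale: "the way of combining these acupoints is often used for strengthening the curative effect".

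Statistical methods sizes the trial for a two-group comparison, a "clinically significant difference of average 20-point reduction on the VAS scores of loudness in acupuncture group" against sham. It adds: "The standard deviation is 25.9 in acupuncture group and 23.8 in the sham-control group". With 80% power and a two-sided 5% level it concludes: "The required sample size is approximately 24 participants for each group".

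**The concern.** The sentence can be read in two ways, and each needs correction. If it is a condition, the trial is presented as a factorial once an interaction fails to show. No test level is given, and nothing says what happens when test and plot disagree. If it is a statement of fact, it settles the result of a trial whose status section says that it is still recruiting. The bracketed example adds a third uncertainty: a factorial presentation normally means the two factor margins, but the example names two single cells.

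On the usual reading, each factor is then reported as an average over the other. The trial's question concerns A against B and A against C. Those contrasts equal the main effects only if there is truly no interaction, and failing to detect one does not establish that. At stake is whether the report can say that the combination beats either set alone, and by how much.

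**Working it through.** **Inputs.** From Statistical methods: difference 20 VAS points; SDs 25.9 and 23.8; 24 per group required, 28 enrolled, 25% withdrawal (28 × 0.75 = 21). Assumed, because the document gives neither: a two-sided 5% level for the interaction test and a true interaction of 20 points. The visual check is left out, since it has no criterion.

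**1. The plan's own figure.** Pooled SD s = √[(25.9² + 23.8²)/2] = 24.87. By the stated formula, n = 2 × [(1.960 + 0.842) × 24.87/20]² = 24.3, which agrees with the stated 24. This is a pairwise calculation; the interaction was not what was sized.

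**2. Standard errors at n = 24 per group.**
- Main effect: s/√n = 5.08
- Pairwise contrast (A-B or A-C): s√(2/n) = 7.18
- Interaction (A-B-C+D): 2s/√n = 10.15

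**3. Power of the interaction test.** For 20 points, z = 20/10.15 = 1.97, so power is Φ(1.97 - 1.96) = 50.4%, or 49.6% by noncentral t with 92 df.

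| Evaluable per group | Interaction | Power (t) |
|---|---|---|
| 21 | 20 | 45% |
| 24 | 20 | 50% |
| 28 | 20 | 56% |
| 24 | 10 | 16% |
| 24 | 30 | 83% |

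With the SD anywhere from 23.8 to 25.9 and n from 21 to 28, the range for 20 points is about 42% to 60%. For 80% power, n = 4 × [(1.960 + 0.842) × 24.87/20]² = 48.6, so about 49 per group.

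**4. What pooling shows after a miss.** In a balanced 2×2 design the main-effect estimates are independent of the interaction estimate, so selecting on a non-significant interaction does not shift their mean.
- *Either set suffices* (A = B = C = 20, D = 0): local main effect = [(20 + 20) - (20 + 0)]/2 = 10, and the same for distal. The true A-B and A-C are 0.
- *Only the combination works* (A = 20, B = C = D = 0): local main effect = [(20 + 0) - (0 + 0)]/2 = 10, and the same for distal. The true A-B and A-C are 20; B-D and C-D are 0.

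**5. How often.** Simulation of the combination-only case (200,000 trials, n = 24): the interaction is missed in 50% of trials. It is missed with at least one main effect significant in 37% of all trials (73% of the misses), and with both significant in 12% of all trials (24% of the misses).

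**6. Power of the direct contrasts at n = 24.** If A exceeds each of B and C by 20 points, z = 20/7.18 = 2.79. Power is about 79% for each contrast and, by simulation, about 67% for both.

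**The case against.** The strongest points on the other side are these.

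- *Pooling is inferred.* The text never says that it averages over the other factor, and its only example names groups B and C. This stands: ambiguity is part of the finding, and the 10-point figures hold only on the usual reading.
- *The 50% is conditional.* This stands. Besides the interaction sizes tabulated, a 10% test level would raise it to about 63%, and a plot that led to more interactions being declared would reduce the misses.
- *The interaction test is not weaker than the main-effect tests here.* True in the combination-only case: the interaction (20) and its standard error are both twice those of the main effect (10), so the power is the same. The complaint is that non-detection carries little information, not that this test is unusually poor.
- *The combination-only case does not give the wrong answer.* A reader might infer that the rule would reverse the conclusion. It would not: two positive pooled effects still point to A above B and A above C. The errors are in size and attribution.
- *Two separate significant effects would often be reported.* A reader might infer this as well, but a miss with both effects significant occurs in only 12% of trials.
- *Detail may sit in a SAP.* That is fair for the branch when an interaction is found, and for a plot used as description. It does not answer a rule that the protocol states, which a SAP following it would inherit.

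**Conclusion.** The point holds as a defect in a stated rule; it should be fixed. The sentence either makes the presentation depend on a check that says little when negative, or presumes its result, and its example does not match a factorial presentation.

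The clearest harm is in the case where either set suffices: at 24 per group a 20-point interaction is missed in about half of trials, and adding the second set then appears to gain about 10 points when it gains none. In the combination-only case the gain is halved and benefit is credited to each set alone, with the direction right.

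These sizes rest on pooled main effects being what is meant, a 20-point interaction, a two-sided 5% test and SD 24.87. The effect of the visual check cannot be quantified. The documents do not support saying that the trial will reach a false conclusion, or that half of all trials would show two significant spurious effects.

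**What to change.** Replace the conditional sentence and correct the bracketed example so that it describes what will be presented. State that, whatever the interaction p-value, the report gives:

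- the four cell means;
- the interaction estimate with 95% CI;
- A-B and A-C, each with 95% CI.

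Base the conclusion on combined versus separate needling on A-B and A-C, and require both to succeed, so that no multiplicity adjustment is needed. Show pooled main effects as supportive, labelled as averages over the other factor. Profile plots may stay as description but should not decide anything.

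The cost is wording and a few contrasts from the same model, with no extra patients; A-B and A-C are the kind of pairwise comparison the trial was sized for. The price is precision: their standard error is 7.18 against 5.08 for a pooled main effect. Requiring both gives about 67% power at 24 per group if A exceeds each of B and C by 20 points, which should be stated openly.

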## Discussion

We have presented the design and the protocol for the randomized controlled trial of acupuncture at local and distant points for subjective tinnitus. Completion of this trial will help to identify whether acupuncture at local acupoints in combination with distal acupoints may be more effective than needling points separately.

It is hoped that this study will encourage renewed interest in acupuncture’s potential for treating people with tinnitus. Recent researches have created a climate where acupuncture might be assumed to be ineffective [17]. However, there is as yet inadequate evidence on which to base a judgment on acupuncture’s effectiveness for tinnitus. Well-designed randomized controlled trials where patients are representative of people with tinnitus in the general population are needed.

In this study, the side-effects of acupuncture will be reported by patients. Several large surveys have also provided evidence that acupuncture is a relatively safe treatment [18]. The results could also provide consumers with information about viable choices. If acupuncture is demonstrated to be effective and safety in tinnitus, there may be a number of patients with these conditions who seek out acupuncture rather than pharmacotherapy.

Patients are informed in a manner suggesting that two different types of acupuncture treatment were compared. One type is traditional, another is new, and the effect of both is uncertain, not mentioning terms such as ‘placebo’ or ‘sham’. Similar strategies of informed consent have been used in most previous acupuncture trials [19].

However, our study has several limitations. Deciding on an appropriate control procedure for clinical studies on acupuncture is a particular challenge [20]. Previous randomized, controlled trials of acupuncture suggest that needling of acupoints is as effective as non-points, in particular for pain releif, although both interventions were more effective than a waiting list control [21-23]. Few guidelines exist, however, for identifying appropriate sham point locations; the depth, direction, and duration of needle insertion; or the need for needle stimulation. In the present study, physicians were instructed to avoid manual stimulation of the needles and provocation of Deqi at non-acupuncture points. However, we cannot rule out that this intervention may have some physiological effects.

One limitation concerns the fact that this is a single-center study. It does not lend the results to great generalizability to more diverse sets of patients in more diverse settings. Our directed acupuncture treatment is uniformly applied, and adjunctive therapies are not used. In addition, acupuncturists in diverse settings with different philosophies, backgrounds, training, and clinical experiences might have chosen different technique for the directed acupuncture intervention. Therefore, the external validity can be somewhat hard to achieve. But we ensure that the risk of contamination between groups will be minimized, while maintaining the integrity of the experimental group comparison. As a result, whether the findings can be generalized to the clinical setting is unclear and more work is needed.

Another limitation is that the therapist is not blinded in the present trial. A blinded study of acupuncture is challenging to conduct because it is almost impossible to blind acupuncturists to the treatments they are delivering. This study does not allow us to determine whether the observed effectiveness is due to placebo effects, intensity of provider contact, or a physiologic effect of needling. Therefore, a bias due to unblinding cannot be ruled out. In addition, the sample size in the present study is relatively small.

## Trial status

The trial is currently in recruitment phase.
